## Abstract

**Background:**

Septic shock has a 90-day mortality risk of up to 50 %. The hemodynamic targets, including mean arterial pressure (MAP) are not based on robust clinical data. Both severe hypotension and high doses of vasopressors may be harmful. Hence, re-evaluation of hemodynamic targets in septic shock is relevant.

**Methods/design:**

The targeted tissue perfusion versus macrocirculation-guided standard care in patients with septic shock (TARTARE-2S) trial is a prospective, two-parallel-group, randomized, open-label, multicenter trial with assessor-blinded outcome evaluation. We will randomize at least 200 patients with septic shock in four European intensive care units (ICUs) to test whether a tissue perfusion-guided treatment strategy based on capillary refill time, peripheral temperature, arterial lactate concentrations, and accepting lower MAP levels, leads to a faster resolution of shock than macrocirculation target-guided standard care.

The primary outcome measure is days alive in 30 days with normal arterial blood lactate (first value of <2 mmol/L) and without any inotropic or vasopressor agent. Secondary outcomes include individual components of the primary outcome, days alive without renal replacement, days alive without mechanical ventilation in 30 days, and new acute kidney injury. The sample size enables detection of a 13.5-h difference in the primary outcome with a type 1 error of 5 % and power of 80 %, assuming 25 % mortality and a mean of 650 h (SD 30) among the 30-day survivors. After 150 included patients the statistician masked for allocation group will recalculate the sample size potentially increasing the sample up to 300. The Data Safety and Monitoring Board (DSMB) will review the safety data after 100 patients.

**Discussion:**

The TARTARE-2S trial will provide important clinical data on treatment targets in septic shock, evaluating the impact of clinical tissue perfusion-guided hemodynamic treatment on a surrogate outcome combining resolution of shock (hyperlactatemia and vasopressors/inotropes), and 30-day mortality.

**Trial registration:**

ClinicalTrials.gov: NCT02579525. Registered on 19 October 2015.

**Electronic supplementary material:**

The online version of this article (doi:10.1186/s13063-016-1515-x) contains supplementary material, which is available to authorized users.

## Background

Septic shock affects millions of people annually and has a 90-day mortality rate of 18 to 50 % [1–5] depending on the patient population and study selection criteria. Early hemodynamic resuscitation and stabilization is considered to be crucial for improved survival. Current resuscitation strategies aim to achieve hemodynamic stabilization as early as possible in order to prevent subsequent organ dysfunction. The guidelines for initial hemodynamic resuscitation of septic shock use primarily macrocirculatory targets, such as mean arterial blood pressure (MAP) and central venous pressure (CVP), and surrogate markers of tissue perfusion such as diuresis. Attempts to use central venous or mixed venous oxygen saturation (ScVO_2_, SvO_2_) to guide resuscitation have been disappointing. Despite early enthusiasm based on a small single-center trial which suggested a major improvement in survival [6], no benefit of ScVO_2_-guided treatment was found in three large multicenter trials [1, 4, 5].

The current SSC guidelines (Surviving Sepsis Campaign: International Guidelines for Management of Severe Sepsis and Septic Shock: 2012) [7] still emphasize a MAP target and to a lesser extent tissue perfusion. Systemic blood pressure and flow and microcirculatory blood flow do not correlate well in septic shock. This is especially true if systemic blood pressure is achieved with vasoconstrictive drugs which per se may impair microcirculation and clinical outcome [8]. Furthermore, a recent systematic review [9] underscored the paucity of clinical evidence to guide the use of vasopressors and to support the current recommendations regarding MAP target levels. In summary, the current resuscitation guidelines for septic shock might direct physicians to use higher doses of vasopressors and inotropes and, thus, facilitate iatrogenic aggravation of shock-induced tissue hypoperfusion.

Impaired tissue perfusion and microcirculation are considered to be hallmarks of septic shock, and increased arterial blood lactate in septic shock is a marker of poor prognosis. These concepts provide a rationale for therapeutic strategies focusing more on improvement of tissue perfusion than systemic hemodynamics. Normalization of elevated blood lactate levels has been proposed to guide resuscitation in septic shock because it may reflect tissue perfusion during shock resuscitation better than strategies based mainly on macrohemodynamic targets. The duration of elevated lactate levels is a clinically relevant surrogate endpoint previously related to robust patient-related adverse outcomes, such as multiple organ dysfunction [10] and mortality [11, 12]. In addition, lactate is also associated with peripheral perfusion [13], and has been used as a target in a previous large study in septic shock in comparison to ScVO_2_-targeted therapy [14]. Abnormal peripheral perfusion, defined as arm-to-fingertip temperature gradient of >4 °C, and capillary refill time (CRT) >4.5 s), is associated with multiple organ dysfunction in critically ill patients [15] and with impaired tissue oxygen saturation and poor outcome in septic shock patients [16]. Of note, subjectively assessed warmness of the peripheral skin has good agreement with the measured temperature differences [15]. The mottling score [17], reflecting perfusion of the knee skin area, has also been used. Additionally, biomarkers (to be explored in sub-studies) indicating endothelial or cardiac damage could elucidate the potential mechanisms leading to untoward clinical patient-related outcomes, such as septic acute kidney injury (AKI) [18] treated with renal replacement therapy (RRT) [19], multiple organ dysfunction, and death.

### Aim

The objective is to compare the feasibility and the effect of resolution of shock of two approaches to the management of tissue hypoperfusion in septic shock: (1) targeted tissue perfusion (TTP) approach versus (2) macrocirculation-guided (MCG) care – the latter reflecting recommended standard care.

## Methods/design

This trial is a prospective, investigator-initiated, multicenter, two-parallel-group, randomized, open-label, multicenter trial of TTP versus MCG care in patients with septic shock (Appendix 1) with adequate generation of allocation sequence, and adequate allocation concealment. Patients will be stratified by center and by the presence/absence of chronic hypertension. Each participating unit will go through an educational program regarding study monitoring methods (including CRT), and study reporting methods (including repeated hemodynamic target assessments and treatment attempts).

The recruitment begins after approval from local ethics committees.

### Ethics committee approvals submission/approval

Bern University Hospital Ethics Committee (Kantonal Ethiko Kommittee (KEK) Bern) 19 October 2015/22 March 2016.

Helsinki University Hospital Operative Ethics Committee – 23 October 2015/16 December 2015.

Rigshospitalet Ethics Committee – April 2016/pending.

### Hypothesis

We hypothesize that targeting clinical tissue perfusion (the TTP arm) will decrease the use and untoward effects of vasopressors, and result in more days alive in 30 days with normal arterial blood lactate (first value of <2 mmol/L) *and* without any inotropic or vasopressor agent – compared to standard clinical care with preference of macrocirculatory targets (the MCG arm).

### Trial interventions

All patients will be treated according to the targets (Appendix 2) of the allocated arm:Intervention group – targeted tissue perfusion (TTP) careControl group – macrocirculatory targets-guided (MCG) standard care

All interventions in both groups will be given at the discretion of the treating clinicians according to the targets. Both the hemodynamic problems detected and the given interventions will be registered at each change of treatment over time (Appendices 3 and 4).

### Concomitant interventions

Treatment of septic shock is complex with multiple interventions [6] and, as blinding of treating personnel is not feasible, the use of several concomitant interventions may be influenced by the allocated intervention arm. In order to minimize these potential differences, treatment suggestions for the following interventions will be provided:Vasopressors – norepinephrine highly recommended (the hemodynamic problems to be registered and reported – Appendix 3)Fluids – correction of hypovolemia (preferably crystalloids, starch not to be used) will be at the discretion of the treating clinician (Appendix 3)Avoidance of excess fluids after 6 h from randomization (amount of given fluids and balance over time up to 72 h will be registered and reported)Inotropic agents – to increase impaired flow, dobutamine is preferred – if ineffective, adrenaline may be usedGlucocorticoids – recommended not to be usedBlood products – red blood cell (RBC) transfusion trigger 70 g/L, unless ischemia or active bleeding [2]Renal replacement therapy (RRT) – suggested criteria according to conventional standard criteria [19, 20], with proven feasibility [21] as follows:serum potassium ≥6.0 mmol/L, orpH <7.20 and serum bicarbonate ≤10 mmol/L, orevidence of severe respiratory failure, based on a PaO_2_/FiO_2_ < 200 and clinical perception of volume overload *and* oliguria, orpersistent severe AKI (serum creatinine remains >50 % the value recorded at randomization) for more than 72 h from randomizationLung-protective ventilation – positive end-expiratory pressure (PEEP) ≥5 cmH_2_O, tidal volume <8 ml/ideal body weight, and plateau pressure <30 cmH_2_O

### Inclusion criteria

Septic shock defined as (Appendix 1):Infection (suspected or documented) *and*Systemic mean blood pressure above 65 mmHg requiring any dose of vasopressors (norepinephrine, epinephrine, vasopressin) despite adequate fluid resuscitation (minimum of 20 ml/kg (actual body weight) crystalloids) *and*Elevated lactate ≥3.0 mmol/L with suspected hypoperfusion

### Exclusion criteria

Age below 18 or over 80 yearsAny other probable condition than sepsis affecting or expected to affect the central nervous system, including post cardiac arrestMyocardial ischemiaAcute pulmonary embolismTerminal illness and not considered for full intensive care supportUse of extra-corporeal membrane oxygenation (ECMO)Known liver disease – Child-Pugh classes B or CKnown chronic kidney diseaseKnown to be pregnant or lactatingMore than 4 h from fulfilled inclusion criteria (to be fullfilled at the latest 4 hours after ICU admission) to randomization (to be done in 8 hours from ICU admission)Other probable cause of hyperlactatemiaPatients transferred from another intensive care unit (ICU)Patients with active hematological malignancy

### Randomization

Randomization will be done using a computer-based algorithm created by an independent statistician, to allow immediate and concealed allocation to the intervention arm. The patients will be stratified according to the site and presence/absence of chronic hypertension (with known medication). A varying block size will be used. Each patient will be allocated a unique patient ID-number. Randomization is targeted to be performed within 2 h after fulfillment of the inclusion criteria in the ICU (but no later than 4 h, the fulfillment of which is an exclusion criterion).

### Primary outcome measure

Days alive in 30 days – with normal arterial blood lactate (first confirmed value of <2 mmol/L *and* without any inotropic or vasopressor agent)

### Secondary outcome measures

Time to normalization of lactateDays alive with normal lactate (all values <2 mmol/L) in 30 daysDays alive without the use of inotropic or vasopressor agents in 30 daysDays alive without RRT in 30 daysDays alive without mechanical ventilation in 30 daysDays alive without any organ support (mechanical ventilation, RRT) in 30 daysNew AKI according to the KDIGO classification (stages I–III)8.. Days alive outside hospital in 90 daysTotal amount of norepinephrine given until day 5Number/total number of the following adverse reactions:ventricular tachycardia/fibrillationatrial fibrillationmyocardial infarctionskin necrosisstrokesecondary bowel ischemialimb ischemiatotal numbers of serious adverse reactions (SAR) (numbers of patients and reactions)

### Exploratory outcomes

All-cause mortality at day 90.

### Blinding

Blinding of health care providers will not be feasible which infers that all clinical staff caring for the patients will be aware of the allocation during the intervention period. The two interventions may lead to different use of concomitant interventions, but the lack of blinding may also result in differences in the use of concomitant interventions during the intervention period. Hence, we will provide suggestions for the use of relevant co-interventions (see “Concomitant interventions”) and will record the use of them.

Information on the primary outcome and other secondary outcomes will be provided by the local investigators from patient charts, but the statistician doing the analyses will be blinded to which intervention the patients received. Information on whether the exploratory outcome of death occurs will be acquired through public registers (the National Civil Registries) without knowledge of which intervention group the patient was allocated to. In Switzerland, the patient or relatives will be contacted. The assessor of the outcomes will be blinded to the study group. The members of DSMB will remain blinded unless they request otherwise.

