### Intervention accountability

Every patient will be allocated a registration sheet to be kept in the site master file. The initials, birth date, screening number, time for randomization, and study arm will be included. The compliance of trial arm targets for each study patient will be checked hourly for the first 72 h, and clinical problems and given hemodynamic treatments will be registered until the study combined endpoint has been fulfilled, up to day 30. The originals for these documents will be kept as the study source data at each site.

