### Data handling

Data will be entered into an electronic, web-based electronic Case Report Form (eCRF) from patient notes by trial personnel. Each patient will receive a unique trial identification number. Trial investigators will receive a personal username and passwords to access the TARTARE-2S trial web-page. Each site will only have access to site-specific data. Data will be handled according to the Swiss, Finnish and Danish laws. All original records (including Informed Consent Forms, eCRFs, and relevant correspondences) will be archived at trial sites for 15 years. The clean electronic trial database file will be delivered to the Inselspital Data Archive and maintained for 15 years and anonymized, if requested by the authorities.

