## Appendix 4 Data to be registered

Data will be obtained in eCRFs from a combination of national registers and medical records. Bedside target list for treatment reasons and decisions will be implemented in the PDMS (*) at each site, if possible.

Baseline variables

- National identification number (if available)
- Sex
- Age at randomization
- Estimated height
- Measured (if not possible estimated) weight
- Comorbidities? Y/N (hypertension*, chronic heart failure*, previous myocardial infarction, previous stroke, chronic obstructive pulmonary disease*, diabetes*, hematological malignancy*, metastatic cancer*, AIDS*)
- Elective or emergency admission*
- Operative or non-operative admission*
- Site of infection (pulmonary/abdominal/urinary tract/soft tissue/other)
- Previous plasma/serum creatinine (7–365 days before hospital admission), if available

24-h from ICU admission:

- Values for Simplified Acute Physiology Score (SAPS II)*

Twenty-four hours before randomization

- Volume of resuscitation fluids (crystalloids, colloids and blood products specified in milliliters)
- Hemoglobin (lowest)*
- SOFA score *variables**

At randomization

- Norepinephrine dose and mean arterial pressure (MAP) at the same time
- Total fluids given in last 2 h
- Lactate (last value from the previous 2 h)

Continuously as 10-min medians in the first 72 h after randomization:

- Systolic arterial pressure*
- Mean arterial pressure*
- Central venous pressure*
- Heart rate*
- Peripheral oxygen saturation (SpO_2_)*
- Continuous central venous oxygen saturation, if available
- Continuous mixed venous saturation, if available
- Dose of norepinephrine*
- Dose of dobutamine*

One-hour intervals (for 72 h)

- Urinary output*
- Volume of given fluids
- CRT – only in the TTP group
- Assessment of upper arm temperature – only in the TTP group
- Assessment of skin mottling score – only in the TTP group

Two-hour intervals (for 72 h unless study endpoint reached)

- Arterial lactate measured in both groups

Four-hour intervals during the first 72 h after randomization (if not discharged from the ICU)

- Arterial blood gas tensions (PaO_2_, PaCO_2_), pH and base excess (BE)
- Calculated Mixed v-aCO_2_/Da-vO_2_-ratio (if pulmonary artery catheter, PAC)
- Cardiac index (if PAC)
- Stroke index (if PAC)

Daily in the first 7 days after randomization (if not discharged from the hospital):

- SOFA score variables*
- Total volume of fluids
- Estimated fluid balance

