If any of the tests presented above must be based on data with more than 5 % missing multiple imputation will be employed. If just one test needs to be based on multiple imputation all tests will be conducted both as complete case analysis and multiple imputation. However, only for tests based on data with more than 5 % missing will the multiple imputation approach constitute the primary analysis. The multiple imputation will be conducted in R using the mice package and the recommendation in accordance with recommendations in the documentation of this package. All outcome variables (secondary and primary), sex, and age as well as stratification and treatment variables will be included in the multiple imputations procedure.

In all tests a *p* value of less than 0.05 will be considered statistically significant. It is noted that as the adaptive sample size recalculation is not depended on a particular value of the treatment effect at the time of recalculation, there is accordingly no need to adjust the significance level to take a possible adjustment of sample size into account. All analyses will be conducted in the statistical software package R. The full statistical analysis will be conducted blinded to actual treatment allocation and a full blinded statistical report produced. Of note, un-blinding will first happen after the full statistical report has been finalized.

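### Outcome evaluation is called assessor-blinded, but the primary outcome is supplied from charts by local investigators who very probably know the arm

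*Protocol article*

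**What the plan says.** The abstract presents the study as an "open-label, multicenter trial with assessor-blinded outcome evaluation". The Blinding section repeats the claim: "The assessor of the outcomes will be blinded to the study group". It does not say who the assessor is or which outcomes are covered.

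The same section also says:
- "all clinical staff caring for the patients will be aware of the allocation during the intervention period".
- "Information on the primary outcome and other secondary outcomes will be provided by the local investigators from patient charts"; the sentence then contrasts this with the blinding of the statistician.
- Death, the exploratory outcome, is taken from civil registries without knowledge of the arm. In Switzerland the patient or relatives are contacted.

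Other sections bear on who knows the arm. Of the registration sheet kept for each patient in the site master file, Intervention accountability says: "The initials, birth date, screening number, time for randomization, and study arm will be included". Under Data handling, the eCRF is completed "from patient notes by trial personnel". Table 2 in Appendix 2 has arm-specific target boxes that are ticked until the study endpoint is reached.

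On the analysis, Appendix 5 says: "The full statistical analysis will be conducted blinded to actual treatment allocation". Appendix 4 lists some items for one arm alone, for example "CRT – only in the TTP group"; upper-arm temperature and mottling score are restricted in the same way.

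**The concern.** In an open-label trial, blinded outcome assessment is the main protection against reporting that favours one arm. Here the primary outcome turns on two times: when lactate is first below 2 mmol/L and when the last inotrope or vasopressor ends. If staff who know the arm determine and report both, readers would credit the primary outcome with a protection that it does not have.

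There is some room for judgement. Primary outcome measure asks for a first confirmed lactate value, while the abstract and the hypothesis speak only of a first value. Lactate is also a treatment target in the TTP arm only (Table 2), so attention to it may differ between arms.

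A second, smaller matter is the statistician's mask. Fields that exist in one arm only would identify the coded groups if they were in the analysis file, and the article names no step that keeps them out.

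**Working it through.** The point rests on no figure in the plan, so there is none to reproduce. The check sets the sections side by side.

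**Step 1: source of each outcome, and whether it is described as blind to allocation.**
- Primary outcome: local investigators, from charts (Blinding). Not described as blind.
- Other secondary outcomes: the same source. Not described as blind.
- 90-day death, Finland and Denmark: civil registries. Described as blind.
- 90-day death, Switzerland: contact with the patient or relatives. Whether the caller knows the arm is not stated.

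No separate assessor or adjudication step is described for the primary outcome.

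**Step 2: do the local investigators know the arm?** No sentence says so outright. But treating staff know it, the registration sheet at the site carries it, trial personnel enter the eCRF from patient notes, and compliance with the arm's targets is checked hourly for 72 h. Hemodynamic problems and treatments are registered until the combined endpoint is met, so site staff must recognise the endpoint as it happens. Knowledge of the arm is a strong inference.

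**Step 3: which records could supply the two times?** For 72 h, Appendix 4 lists norepinephrine and dobutamine doses as 10-minute medians and lactate every 2 h in both arms. Later it lists vasopressor and inotrope use as a daily yes/no. Treatment changes are still registered up to day 30 (Intervention accountability), but on site-completed sheets.

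The plan's own log-normal assumption (Sample size and power) shows how many survivors would resolve after 72 h, taking the time as one unbroken run from randomization:
- Control, mean 70 h, SD 30: σ² = ln(1 + (30/70)²) = 0.1686, σ = 0.4106, μ = ln 70 − 0.1686/2 = 4.164. z = (ln 72 − 4.164)/0.4106 = 0.274, upper tail about 39 %.
- TTP under the planned 18 h effect, mean 52 h, SD 30: σ² = ln(1 + (30/52)²) = 0.2873, σ = 0.5360, μ = ln 52 − 0.2873/2 = 3.808. z = (ln 72 − 3.808)/0.5360 = 0.875, upper tail about 19 %.

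A daily field places an end time only within 24 h, which is wider than the 18 h effect. A material share of survivors would therefore depend on other records, including sheets kept by unblinded staff. This describes the data source and does not estimate a bias.

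**Step 4: what does the statistician need?** The tests in Appendix 5 cover the primary, secondary and exploratory outcomes. The imputation model uses all primary and secondary outcomes, sex, age, stratification and treatment variables. Capillary refill time, temperature, mottling and MAP appear in neither. Total norepinephrine to day 5 (outcome i) appears in both, and the hypothesis expects less vasopressor use in TTP. It can hint at which coded group is TTP.

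**The case against.** The Blinding section separates those who provide information from the assessor of the outcomes. These may be different people, and a condensed article may leave the assessor's identity to the full protocol. The section also openly discloses unblinded care and chart-based reporting. Much of the outcome is hard data: death, a laboratory value and recorded drug doses. Decisions to stop drugs are made by unblinded clinicians, and no blinded abstraction can cure that.

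Most of this is fair. It limits the likely harm and rules out saying that no blinded assessor exists. It does not reconcile the two statements: an assessor who works from information selected and timed by open-label sites gives limited protection, and no allocation-free route is described for the primary outcome.

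Three stronger readings are tempting and are not supported:
- **That the statistician necessarily sees the TTP-only fields.** Appendix 4 lists what is registered, not what is in the analysis file, and no planned test needs these fields. They could reveal the arms only if included.
- **That the sample size recalculation is unmasked.** It uses the observed mortality proportion and the observed dispersion of the primary outcome, and neither is a comparison of arms.
- **That a bias of some number of hours is shown.** Any shift set against the planned 18 h would be an arbitrary illustration.

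**Conclusion.** The point holds for the primary outcome: the article claims assessor blinding but describes a data route that does not deliver it. Allocation-blind ascertainment is described for one exploratory outcome, and explicitly for registries only. The conclusion assumes that the local investigators who report the outcomes know the arm, which is very probable but not stated in so many words. The size of any resulting bias cannot be derived from the documents.

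For the analysis, the supportable statement is narrower: the TTP-only fields and MAP could unmask the coded groups if supplied, norepinephrine totals may hint at them, and the article names no safeguard. The wording and the data handling should be corrected. The sample size is not affected.

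**What to change.** 1. Limit the blinding claim to registry-based death and the coded analysis. State that ascertainment of the primary outcome is open-label, unless its two times are determined from allocation-free data.
2. Derive both times by one fixed rule from time-stamped laboratory and infusion records: the electronic patient data system where available, the hourly or daily record otherwise. The rule should settle whether the lactate value must be confirmed. State that this limits reporting bias but not bias from open-label decisions to stop drugs.
3. Leave capillary refill time, skin temperature, mottling and MAP out of the statistician's coded file until the blinded report is final.
4. Acknowledge that total norepinephrine may hint at the TTP group. Keep it available, because Appendix 5 puts all outcomes into the imputation model, and fix the analysis code for the primary outcome before this variable is compared by arm.

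The cost is protocol wording, an extraction rule and a file split. The downsides are a less favourable description of blinding and adherence results that come in a second step.
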